A new programme of NHS Health Checks (NHSHC) was introduced in the UK in 2009. This aims to provide cardiovascular risk assessment every five years for adults aged 40-74 who are not already diagnosed with CVD or diabetes. The NHSHC offers a promising strategy for preventing CVD, yet several concerns have been raised in relation to its uptake, cost-effectiveness, success in reducing diseases and effectiveness of risk management. In this context, evaluation of the programme’s longer-term outcomes is crucial. This study aims at evaluating changes in risk and cardiovascular clinical events and mortality outcomes following uptake of a health check. We will use a matched cohort design in the CPRD by comparing participants with a record of a complete NHSHC between 1st of April 2010 and 31st of March 2013 with follow-up data available for a minimum of three years after their health check up to 31st March 2016, together with matched control participants who did not receive a health check. We will adopt a time-to-event framework with date of check as the start date to evaluate the onset of new prescriptions. Hazard ratios will be estimated using the cox proportional hazards model and incident rate ratios using Poisson regression to examine the association between the programme and changes in clinical events and mortality.

1. **Objectives, Specific Aims and Rationale**

**Aim:** To measure the long term outcomes of the NHS Health Checks programme and evaluate whether outcomes following an NHS Health Check are more favourable than in controls.

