**Objectives:**

1. To test the hypotheses that greater changes in CVD risk factors, CVD risk score and CVD risk management follow the NHS Health Check than are observed in control participants;
2. To test the hypothesis that all-cause mortality and the incidence of clinical events (new diagnoses of ischaemic heart disease, stroke, diabetes mellitus and chronic kidney disease) may be lower in participants who received NHS Health Checks than control participants;
3. To test the hypothesis that inequalities in the outcomes of Health Checks across deprivation category may be lower in NHS Health Check participants than in control participants.
4. **Background**

Cardiovascular disease is the leading cause of death worldwide and in the United Kingdom (1). Almost 155,000 deaths annually are caused by CVD in UK, accounting for more than a quarter of all deaths (2). Diabetes also is increasing in frequency, with four million people in UK living with diabetes, which is associated with serious complications leading to disability and premature mortality (3).The NHS Health Check (NHSHC) is a primary prevention programme that was introduced in England. The programme targets individuals aged 40 to 74 years, who have not yet developed CVD and are not treated for elevated risk, and estimates their risk of heart disease, stroke, type 2 diabetes, chronic kidney diseases and some forms of dementia (4). After identifying individuals at elevated risk, a personalised risk management intervention is provided. This programme provides an opportunity in terms of addressing multiple risk factors which, if successful, might reduce the risk of several diseases. Results from the Department of Health economic model suggested that the NHS Health Check could save 650 lives, and 1600 heart attacks and 4000 cases of diabetes could be prevented a year (5).

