The original sample was extracted from the October 2014 release of CPRD for 140,356 participants with a record of an NHS Health Check between 1 April 2010 and 31 March 2013, from 452 general practices in England. We restricted the sample to all 106,784 participants registered with 334 general practices with IMD 2010 quintile for England, linked via the participant postcode, at the lower super-output area level. We also excluded all patients who were ever treated with antihypertensive drugs (8531) or statins (1529) before the date of the check. We also excluded patients (4859) who did not have a full year of up to standard record before the date of the check and one patient whose check was after 31 March 2013. We also excluded patients with diabetes (227), coronary heart disease (2) or stroke (3) diagnosed before the check. There remained 91,618 participants who had a health check between 1 April 2010 and 31 March 2013, who had at least 12 months record, were never treated with antihypertensive drugs or statins, and were not diagnosed with diabetes, stroke or CHD before the check. For these 91,618 participants, eligible control participants were identified for 75,123 (82%) and these participants, and their matched controls, will be included in the present study.

1. **Selection of comparison group(s) or controls**

Control participants were selected if they were eligible for the NHS Health Checks but did not receive the check, they might have been invited to attend the Health Check, or not. The control participants were individually matched by general practice, gender and age with participants who received the Health Check.

1. **Exposures, Outcomes and Covariates**

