Primary outcomes: Data will be analysed for changes in all-cause mortality and CHD and stroke clinical events, diabetes diagnosis and chronic kidney disease (CKD) diagnosis. The Read codes used to identify cases of CHD in CPRD data will be those listed in reference 9. The Read codes used to identify cases of stroke in CPRD data will be those listed in reference 10. (9, 10) , while ICD-10 codes will be used in HES data. Where feasible stroke will be classified as haemorrhagic or ischaemic. CHD events will be classified as angina, myocardial infarction, coronary artery bypass surgery or percutaneous coronary intervention and other. To identify cases of diabetes, diabetes drug prescriptions will be analysed by mapping drug codes to chapter subheadings in the British National Formulary (6.1 for drugs used in diabetes). Medical diagnosis codes and levels of HbA1c levels (6.5%) will be analysed as well to identify diabetes diagnosis. Medical diagnosis codes and levels of serum creatinine will be used to identify CKD cases. (11) . Details of proposed case definitions are given in Table 1.

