**Table 1: Case definitions for key measures:**

| **Condition** | **Read Codes** | **Therapy Codes** | **Test results** | **ICD-10 codes** |
| --- | --- | --- | --- | --- |
|  |  |  |  |  |
| **Ischaemic heart disease** | As listed in reference 9. | N/A | N/A | I20-I25 |
|  |  |  |  |  |
| **Stroke** | As listed in reference 10. | N/A | N/A | I60-I64 |
|  |  |  |  |  |
| **Diabetes mellitus** | As listed in Appendix 1. | BNF chapter 6.1.1 and 6.1.2 | HbA1c >=6.5% (48 mmol/mol) | E10-E14 |
|  |  |  |  |  |
| **Chronic kidney disease** | K05 and K06 codes | N/A | eGFR based on serum creatinine using CKD-EPI equation (11) | N18, N19 |
|  |  |  |  |  |

Secondary outcomes: CVD risk and CVD risk factors, including: smoking, BP, total cholesterol, HDL and BMI. Data on medication prescription for antihypertensive drugs, lipid-lowering drugs, antiplatelet drugs and nicotine replacement therapy will be analysed by recording drug codes to chapter subheadings in the British National Formulary (chapter 2 for CVD drugs).

1. **Data/ Statistical analysis**

The proportion of participants with values recorded for five risk factors (blood pressure, total cholesterol, HDL, BMI and smoking status) will be evaluated. Risk factor values will also be assessed. Changes over time in prescription of drugs for CVD risk management, including antihypertensive, lipid-lowering, antiplatelet and nicotine replacement therapy, will be evaluated.

The association between NHSHC and changes in CHD, stroke, diabetes and CKD clinical events will be examined using Cox hazard and Poisson regression models. Person-time approach will be adopted, where the start date is the date of the check. Hazard ratios will be estimated using Cox proportional hazards models and incident rate ratio using Poisson regression model. The proportional hazard assumptions will be tested. Linear mixed models will be used to study changes in continues outcomes (BP, cholesterol and BMI measurements). Follow-up will be censored if a control participant receives a health check at a later date. The effect of deprivation will be evaluated. Potential effect modification from deprivation category will be evaluated by testing for an interaction of health check status and deprivation category.

1. **Plan for addressing confounding**

To control for potential cofounders, model covariates will include age, gender, ethnicity and deprivation indices.

1. **Plan for addressing missing data**

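### CKD recorded before the check is not excluded, although new CKD is a primary outcome, and no rule stops it being counted as an incident event

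*Protocol*

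**What the plan says.** Under Study Population the protocol lists the exclusions with counts: earlier antihypertensive or statin treatment, less than a year of adequate record, one check outside the window, and then "We also excluded patients with diabetes (227), coronary heart disease (2) or stroke (3) diagnosed before the check". The description of the resulting group says that its members "were not diagnosed with diabetes, stroke or CHD before the check". CKD is in neither place.

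For controls, the comparison-group section says "Control participants were selected if they were eligible for the NHS Health Checks but did not receive the check". The Technical Summary describes the eligible adults as those "who are not already diagnosed with CVD or diabetes", and the Background adds that they are not treated for elevated risk. Neither account names CKD.

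Objective 2 concerns "new diagnoses of ischaemic heart disease, stroke, diabetes mellitus and chronic kidney disease". The primary outcomes include "diabetes diagnosis and chronic kidney disease (CKD) diagnosis", and on ascertainment the protocol says "Medical diagnosis codes and levels of serum creatinine will be used to identify CKD cases". For CKD, Table 1 gives the K05 and K06 Read codes, ICD-10 N18 and N19, and an eGFR calculated by the CKD-EPI equation. The HbA1c entry in the same table has a cut-off; the eGFR entry has none. The analysis section starts person-time at the check.

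**The concern.** A time-to-event analysis of new disease needs people who are free of that disease at time zero. For diagnosed diabetes, CHD and stroke the cohort meets this condition by construction. For CKD it does not. The cohort is taken over unchanged from a previous study of risk factor detection, and CKD is a primary outcome here without a risk set of its own.

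Someone with CKD on record before the check could therefore become a case at the next CKD code or low eGFR. The CKD hazard ratio would then mix old disease with new, while Objective 2 asks about new diagnoses only. The health check cannot prevent disease that was already there, so such cases carry no information on the hypothesis.

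**Working it through.** **1. The protocol's own figures.** The only power statement is for CHD; there is none for CKD.

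- Three-year control risk: 3 × 0.003 = 0.009. With a risk ratio of 0.85, the health check risk is 0.00765.
- Expected events: 75,000 × 0.00765 + 182,000 × 0.009 = 573.75 + 1,638 = about 2,212.
- Two-sided power at 0.05 is 92.7% by comparison of proportions and 93.5% by the Schoenfeld formula. The stated figure of more than 90% reproduces, and the present point does not affect it.

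Cohort flow: 106,784 − 8,531 − 1,529 − 4,859 − 1 − 227 − 2 − 3 = 91,632, against 91,618 stated. The protocol does not explain the difference of 14 or link it to CKD.

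**2. Is there a rule elsewhere?**

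| Place in the protocol | Bearing on prior CKD |
|---|---|
| Study Population, exclusion list and final description | Not named |
| Control selection and programme eligibility | Not named |
| Objective 2 | Calls the diagnoses new; gives no rule |
| Table 1 | No eGFR cut-off, no baseline condition, no persistence condition |
| Analysis section | Time starts at the check; no washout |
| Confounding plan | Age, gender, ethnicity and deprivation; not baseline kidney function |
| Missing data plan | Unrecorded clinical events are taken not to have happened |

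No entry removes earlier CKD from the CKD risk set.

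**3. Illustration of size. The rates are assumed; none is in the protocol.** Let π be baseline CKD prevalence (0.5% to 3%), I three times the annual incidence (3 to 5 per 1,000), R the true risk ratio, and h and c the fractions of prevalent cases that are recorded after the index date in health check and control participants. Incident cases are taken as fully recorded in both groups.

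Apparent ratio = [πh + (1 − π) × I × R] / [πc + (1 − π) × I]

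*Equal re-recording (h = c = 1).* With π = 0.01, I = 0.015 and R = 0.85: (0.01 + 0.01262) / (0.01 + 0.01485) = 0.91. Over the whole assumed range:

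- Prevalent cases number 376 to 2,254 among 75,123 health check participants and 911 to 5,467 among 182,245 controls.
- They form 25% to 78% of control events.
- A true ratio of 0.85 appears as 0.89 to 0.97.

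*More recording in attenders (h, c = 0.6, 0.3 or 0.8, 0.4).* With π = 0.01, I = 0.015, h = 0.6 and c = 0.3:

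- R = 1.00 gives (0.006 + 0.01485) / (0.003 + 0.01485) = 1.17.
- R = 0.85 gives (0.006 + 0.01262) / (0.003 + 0.01485) = 1.04.

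Over the whole range, a true ratio of 1.00 appears as 1.09 to 1.58, and 0.85 as 0.96 to 1.52.

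**The case against.** The strongest reply is that the protocol nowhere says that prevalent CKD will be counted. Objective 2 speaks of new diagnoses, which could lead an analyst to drop people with an earlier CKD code, and outcome-specific risk sets are often left to an analysis plan. The listed disease exclusions also look like programme eligibility criteria carried over with the cohort, so CKD's absence from them does not prove that it was left out of the CKD risk set. Nor is the contrast with the other diseases complete: only diagnosed diabetes is removed, while Table 1 also accepts an HbA1c result, so undiagnosed diabetes is in a similar position.

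Much of this stands, and it limits what can be claimed. A reader might infer that pre-existing CKD is definitely counted as incident; the text shows only that no rule prevents it. A reader might also infer that attenders have kidney function measured on the day of the check, so that the error falls mainly on them. The protocol does not say so: the five risk factors it lists include lipids but not creatinine. It does describe the programme as estimating CKD risk, which makes extra kidney testing plausible and no more.

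The reply does not remove the point. The protocol itself fixes cohort entry and case definitions, and the word new does nothing about an earlier low eGFR that was never coded.

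**Conclusion.** The point holds as a gap in the CKD risk set: followed as written, the protocol allows CKD recorded before the index date to count as an incident primary outcome event. It should be corrected, but it touches one outcome and leaves the others and the CHD power statement intact.

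The size cannot be derived from the protocol. Equal re-recording in both groups dilutes the ratio towards 1. More kidney testing in attenders pushes it upwards, and above 1 if the check has no true effect, which runs against the hypothesis of Objective 2. The ranges shown rest on assumed prevalence, incidence and recording. Prevalence could be lower than assumed, because the cohort drops 8,531 + 1,529 = 10,060 people treated with antihypertensives or statins.

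A reader might compute that 40% to 67% of attenders' new CKD is old disease: 751 / (751 + 1,127) and 2,254 / (2,254 + 1,127), from 1% to 3% prevalence and 5 per 1,000 per year. That is an upper bound which needs every prevalent case to be re-recorded. On the same terms it applies to controls, for example 1,822 / (1,822 + 2,734) = 40%, so it is no evidence of an excess in attenders.

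**What to change.** For the CKD analysis only, exclude from both groups anyone with a K05/K06 or N18/N19 code, or an eGFR meeting the study's CKD case threshold, recorded strictly before the index date. That date is the date of the check or, for controls, the matched date, which the protocol should state. Do not exclude on index-date results: if the check prompts testing, such a rule would remove newly found CKD from attenders alone and favour the health check.

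State the eGFR case threshold, and require a test-based case to rest on a repeated low value. Add a sensitivity analysis using coded diagnoses only, because exclusion on earlier records cannot remove CKD in people who were never tested, and any difference in testing between the groups would remain.

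The exclusion uses records already held. The cost is a slightly smaller CKD risk set and fewer test-defined cases; the cohort for all other outcomes is unchanged.

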**Sample power calculation:**

Assuming that the background incidence of CHD is about 3 per 1,000 per year and the type 1 error rate is set at 0.05, if there are 75,000 health check participants and 182,000 control participants, there will be more than 90% power to detect a risk ratio of 0.85, for reduction of CHD incidence, over three years of follow-up.

1. **Data Linkage Required (if applicable)**

We have requested linkage to the Index of Multiple Deprivation data to test whether the outcomes of the NHS Health Checks differ across different socioeconomic status. We already have deprivation data obtained for protocol 13_071A but we will request all linked data again from the latest linkage Set (i.e. Set 12). This will ensure that we are working with the most accurate and consistent data (e.g. if a patient's postcode has been added or changed).

In addition, we are requesting ONS mortality data to enable cause of death analysis. We also plan to use integrated HES data to evaluate hospital admissions with ischaemic heart disease or stroke events. We are aware that a small number of patients may be eligible for linkage to IMD data but not eligible for linkage to the ONS mortality and inpatient HES data. This is because eligibility for linkage to IMD depends on the availability of a valid postcode, whereas eligibility for linkage to ONS and HES data depends on availability of a valid NHS number.

We will initially conduct the analysis using CPRD data only (the ‘unlinked analysis’). Subsequently, we will conduct a similar analysis using CPRD data together with linked data (the ‘linked analysis’). We will take into account the coverage period for the ONS mortality and inpatient HES data. Set 12 linkages provide ONS mortality and inpatient HES data through to 30/09/15, so the time period for the linked analysis will be restricted in comparison to the unlinked analysis. Patients who are not eligible for ONS and HES linkage will be excluded from the linked data analysis by restricting the study population to those eligible for all linkages. The loss of participants should not be large because the initial sample was drawn from linkage eligible participants.

1. **Study Population**

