Recording of risk factor values is an outcome of importance in respect of evaluating NHS health checks. Prescriptions, clinical events and deaths that are not recorded will be presumed to be absent, because recording of these measures is expected to be complete.

1. **Limitations of the study design, data sources and analytical methods**

A randomised evaluation would provide the optimal study design but as health checks are part of a national policy, the present non-randomised design will offer an achievable study design. We expect a high level of completeness for recording of NHS health checks because use of mandated Read codes is used for reimbursement of practices. We acknowledge that there may be lack of standardisation of blood pressure measurements and recording of measures such as smoking and body mass index may be subject to misclassification. Use of diagnostic codes for CVD events varies between general practices and some clinical events are recorded with codes that lack precision.

1. **Patient or user group involvement (if applicable)**

Patients have not contributed to the development of this protocol but we have engaged with patients in our health check evaluation work and will be able to discuss the results of this study with patient groups.

1. **Plans for disseminating and communicating study results, including the presence or absence of any restrictions on the extent and timing of publication**

The results of this study will be reported in national public health events and we will also prepare peer review paper for publication. It will also contribute to a PhD thesis.

1. **References**

| Medcode | ReadCode | ReadTerm | Type |
| --- | --- | --- | --- |
| 506 | C100112 | Non-insulin dependent diabetes mellitus | 2 |
| 608 | 66A2.00 | Follow-up diabetic assessment | 2 |
| 711 | C10..00 | Diabetes mellitus | 2 |
| 758 | C10F.00 | Type 2 diabetes mellitus | 2 |
| 1038 | C100011 | Insulin dependent diabetes mellitus | 1 |
| 1323 | F420.00 | Diabetic retinopathy | 2 |
| 1407 | C10FJ00 | Insulin treated Type 2 diabetes mellitus | 2 |
| 1549 | C10E.00 | Type 1 diabetes mellitus | 1 |
| 1647 | C108.00 | Insulin dependent diabetes mellitus | 1 |
| 1682 | C101.00 | Diabetes mellitus with ketoacidosis | 1 |
| 1684 | 66A4.00 | Diabetic on oral treatment | 2 |
| 2340 | F381311 | Diabetic amyotrophy | 2 |
| 2342 | F372.12 | Diabetic neuropathy | 2 |
| 2378 | 66AJ.00 | Diabetic - poor control | 2 |

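### As worded, the CHD and stroke outcomes do not count ONS-registered deaths from these causes, so first events fatal outside hospital and not coded by the GP can be missed

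*Protocol*

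**What the plan says.** The section on exposures, outcomes and covariates sets the sources. For CHD: "The Read codes used to identify cases of CHD in CPRD data will be those listed in reference 9". For stroke: "The Read codes used to identify cases of stroke in CPRD data will be those listed in reference 10". It then adds "while ICD-10 codes will be used in HES data". CHD events are to be classed as angina, myocardial infarction, revascularisation procedures or other; coronary death is not named. Table 1 gives I20-I25 for ischaemic heart disease and I60-I64 for stroke, in an ICD-10 column that names no data source.

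The data linkage section gives the two linked sources different jobs. For HES: "We also plan to use integrated HES data to evaluate hospital admissions with ischaemic heart disease or stroke events". For ONS: "we are requesting ONS mortality data to enable cause of death analysis". The only death outcome in the objectives or the outcomes section is all-cause mortality.

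The order of work is also stated: "We will initially conduct the analysis using CPRD data only". A similar analysis with the linked data follows, ending on 30/09/15, when HES and ONS coverage stops.

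The missing-data section presumes that unrecorded prescriptions, clinical events and deaths did not occur, "because recording of these measures is expected to be complete". The limitations section notes that use of CVD diagnostic codes varies between practices and that "some clinical events are recorded with codes that lack precision".

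**The concern.** A CHD or stroke outcome built from GP codes and hospital admissions has a known gap: the person whose first event is a death before admission. Such a person has no admission to find, and has a GP event code only if the practice enters one after the death. The death registration is the natural third source. Here it is requested, but it is tied to an analysis with no matching outcome.

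Combined with the presumed-absent rule, the gap has a definite effect. The person contributes time up to death and then leaves the CHD or stroke analysis without an event. These are the most severe events that a prevention programme aims to avert. Leaving them out costs events. It would also shift the estimate if the effect of the health check on them differs from its effect on non-fatal events, or if the two groups differ in how often they are captured.

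**Working it through.** **Which source catches which event, as the text stands**

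| First event | CPRD-only analysis | Linked analysis |
| --- | --- | --- |
| Non-fatal, coded by the GP | counted | counted |
| Admitted, not coded by the GP | not counted | counted through HES |
| Fatal outside hospital, coded by the GP | counted | counted |
| Fatal outside hospital, not coded by the GP | not counted | not counted in CHD or stroke by any stated rule; counted in all-cause mortality |

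ONS data could close the last row in the linked analysis only. The CPRD-only analysis uses neither HES nor ONS.

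**Reproducing the stated power**

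Inputs from the sample power calculation: 75,000 checked, 182,000 controls, 3 CHD events per 1,000 per year, three years, risk ratio 0.85, type 1 error 0.05. Two-sided testing is my assumption, as the protocol does not state the sides.

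- Expected events, controls: 182,000 × 0.003 × 3 = 1,638.
- Expected events, checked: 75,000 × 0.003 × 3 × 0.85 = 573.75.
- SE(log RR) = √(1/573.75 + 1/1,638) = 0.0485.
- z = |ln 0.85| / 0.0485 = 0.1625 / 0.0485 = 3.35.
- Power = Φ(3.35 − 1.96) = 91.8%.

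A two-proportion formula gives 92.7% and the Schoenfeld formula 93.5%. The protocol's claim of more than 90% is reproduced.

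**If a share f of CHD events is missed**

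Assume that 3 per 1,000 includes the missed deaths, that the share is the same in both groups, and that the risk ratio is 0.85 for missed and captured events alike. Both event counts scale by (1 − f), so z becomes 3.35 × √(1 − f). The values of f are assumptions, since the documents give none.

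| f | Events, checked / control | z | Power |
| --- | --- | --- | --- |
| 0 | 574 / 1,638 | 3.35 | 91.8% |
| 5% | 545 / 1,556 | 3.27 | 90.4% |
| 10% | 516 / 1,474 | 3.18 | 88.8% |
| 20% | 459 / 1,310 | 3.00 | 85.0% |
| 30% | 402 / 1,147 | 2.80 | 80.0% |

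The two-proportion formula gives 89.9% at 10% and 86.1% at 20%. Power falls below 90% at f of about 6% by the log risk ratio formula and about 10% by the two-proportion formula.

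**If the effect on the missed deaths differs**

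Let the risk ratio over all events be 0.85 and the risk ratio for the missed deaths be r, where f is the share missed among controls. The captured events then show (0.85 − f × r) / (1 − f).

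- f = 20%, r = 0.70: (0.85 − 0.14) / 0.80 = 0.8875, power 60.9%.
- f = 20%, r = 1.00: (0.85 − 0.20) / 0.80 = 0.8125, power 96.4%.

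The estimate can move either way. Nothing in the documents says which way, or that it moves at all.

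**The case against.** The strongest reply is that the protocol never says HES is the sole ICD-10 source. Table 1 names no source, the linked analysis uses CPRD together with the linked data, and those data include ONS. A reader might infer that ONS deaths are excluded, or that every out-of-hospital death is lost. Neither follows. Counting ONS deaths is left unstated rather than ruled out, and Read codes run in parallel, so a GP may code a fatal infarction or stroke. This stands, and it is why the point is that such events can be missed. It does not remove the point, because the only sentence that assigns ICD-10 codes to a source names HES, and ONS is given a different task.

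Second, Objective 2 pairs new diagnoses with all-cause mortality, so these deaths do count in a primary outcome. That is true, but they do not count in the outcomes for CHD and stroke.

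Third, the power figures rest on assumed shares. If 3 per 1,000 is already a rate of recorded events, the stated power is unaffected. The calculation also uses three years, whereas checks from 1 April 2010 to 31 March 2013 followed to 31 March 2016 allow three to six years before censoring. Both points stand, so the figures are illustrative only.

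Fourth, a reader might infer bias from more GP contact, and so more event recording, among checked people. The documents do not show this. Controls are matched within practice, and the earlier study by the same team reported risk-factor detection, not event coding. Adding ONS deaths would in any case not correct differential coding of non-fatal events.

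Fifth, the limitations section speaks of variable and imprecise codes, not of absent events. It sits uneasily with the completeness premise but does not contradict it.

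**Conclusion.** The point holds as a gap in the case definitions for two primary outcomes. Followed as written, the protocol treats a first coronary death or fatal stroke with no admission and no GP code as no event, while obtaining the data that would identify it. Because the protocol itself assigns the sources, this is more than detail left for a later plan.

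The size is unknown. On the assumption that the planning rate includes these deaths and that the risk ratio is constant, missing 10% to 20% of CHD events takes power from about 92% to between about 89% and 85%. That is a modest loss of precision. Bias requires capture or effect to differ between the groups, which is possible but not shown.

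Two stronger readings are not supported. One is that the stated power is wrong: it reproduces. The other is that the linked analysis must become the main one. That choice is a trade-off: with follow-up ending on 30/09/15, a check on 31 March 2013 has 2.5 years, short of the three-year minimum that the protocol promises.

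**What to change.** In the outcomes section and Table 1, state that in the linked analysis a death with ONS underlying cause I20-I25 counts as a CHD event and one with I60-I64 as a stroke event, dated at death when no earlier event is recorded. Name the data source for the ICD-10 column of Table 1.

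In the missing-data section, limit the completeness statement: say that the CPRD-only analysis can miss first events that are fatal outside hospital and not coded by the GP, and that the linked analysis adds ONS deaths for this reason.

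The cost is a few sentences and a few lines of code on data already requested. The downsides are some misclassification of certified cause of death, and that the remedy cannot reach the CPRD-only analysis or any event after 30/09/15.

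### The CHD and stroke definitions name GP Read codes and HES codes but not the ONS cause of death, so a fatal first event with no GP or HES code would not count in either outcome

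*Protocol*

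**What the plan says.** Under Exposures, Outcomes and Covariates, the protocol lists five primary outcomes: all-cause mortality, CHD, stroke, diabetes and CKD. CHD and stroke cases come from Read code lists given in two references, "while ICD-10 codes will be used in HES data". The CHD sub-types are angina, myocardial infarction, revascularisation and other, with no fatal category. Table 1 gives the ICD-10 ranges I20-I25 and I60-I64 in a column that names no data source.

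Data Linkage Required gives the two linked sources separate purposes. For HES: "We also plan to use integrated HES data to evaluate hospital admissions with ischaemic heart disease or stroke events". For ONS: "we are requesting ONS mortality data to enable cause of death analysis". An unlinked analysis comes first, followed by a similar analysis that adds the linked data, limited to patients eligible for all linkages and to data up to 30/09/15.

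The missing-data section treats clinical events and deaths that are not recorded as not having happened.

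**The concern.** A person whose first coronary or cerebrovascular event is a death outside hospital may have no GP or HES code for it. ONS would hold the cause, but the event definitions do not draw on ONS. The most severe first events could therefore be left out of the two outcomes they bear on most directly, although the data set that would identify them has been requested.

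Two things are at stake. The first is information: fewer CHD events, and CHD is the only outcome with a power calculation. The second is interpretation: the CHD and stroke ratios would describe coded events only. If the check changed how often these deaths carry a code, or affected fatal first events differently from the rest, the reported ratio would differ from the ratio for all first events.

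**Working it through.** **1. Sources side by side**

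| Source | Role stated in the protocol | Feeds CHD/stroke events? |
|---|---|---|
| CPRD Read codes | case identification | yes |
| HES ICD-10 codes | admissions with IHD or stroke | yes |
| ONS mortality | cause-of-death analysis | not stated |

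All-cause mortality is the only mortality outcome listed, so no listed outcome uses the cause of death.

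**2. The stated power**

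Inputs, all from Sample power calculation: "Assuming that the background incidence of CHD is about 3 per 1,000 per year"; "the type 1 error rate is set at 0.05" (sidedness is not stated, two-sided used here); "if there are 75,000 health check participants and 182,000 control participants"; "there will be more than 90% power to detect a risk ratio of 0.85"; "over three years of follow-up".

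Expected events over three years:
- health check: 75,000 × 0.009 × 0.85 = 573.75
- control: 182,000 × 0.009 = 1,638
- total: 2,211.75

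Power by three methods:
- Log rate ratio: SE = √(1/573.75 + 1/1,638) = 0.0485; |ln 0.85| = 0.1625; Φ(0.1625/0.0485 − 1.96) = 91.8%.
- Two proportions, 0.00765 against 0.009: 92.7%.
- Schoenfeld, with 75,000/257,000 = 0.292 exposed: Φ(√(2,211.75 × 0.292 × 0.708) × 0.1625 − 1.96) = 93.5%.

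All three agree with the stated figure.

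**3. Sensitivity to missed events**

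Assumptions: the 3 per 1,000 counts all first CHD events, and a share f is missed equally in both groups. The documents give no value for f.

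| f | Events | Log ratio | Two proportions | Schoenfeld |
|---|---|---|---|---|
| 0 | 2,212 | 91.8% | 92.7% | 93.5% |
| 5% | 2,101 | 90.4% | 91.4% | 92.3% |
| 10% | 1,991 | 88.8% | 89.9% | 90.9% |
| 20% | 1,769 | 85.0% | 86.1% | 87.5% |
| 25% | 1,659 | 82.7% | 83.8% | 85.3% |

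Power reaches 90% at f of about 6.4% (log ratio), 9.7% (two proportions) and 13.0% (Schoenfeld: 1,925 events needed, 1 − 1,925/2,211.75). If the 3 per 1,000 is already a rate of coded events, there is no loss.

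**4. Effect on the ratio**

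- *Equal loss, same effect on all first events.* Both rates are multiplied by (1 − f), so the ratio is essentially unchanged.
- *Unequal capture (illustration).* The true ratio is 1.0, and a share d = 0.25 of these deaths in attenders carries an earlier code because of the check, with none extra in controls. Observed ratio = (1 − f + f × d)/(1 − f): 1.03 at f = 10%, 1.06 at 20%, 1.08 at 25%.
- *Different effect (illustration).* The check acts only on fatal first events, with ratio 0.7. The all-event ratio is (1 − f) + 0.7f: 0.97, 0.94 and 0.925 for the same f, while the captured ratio is 1.00. With f = 20% and a ratio of 0.85 for other events, a fatal ratio of 0.70 or 1.00 gives an all-event ratio of 0.82 or 0.88, while the captured ratio stays at 0.85.

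The values of f, d and the fatal ratio are assumptions with no source in the documents.

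**The case against.** The case against has several parts, and much of it stands.

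- *ONS may be intended.* Table 1's ICD-10 column names no source, and the linked analysis is described as using the linked data and is limited to ONS and HES coverage. But the outcome text, which points to Table 1 for detail, mentions ICD-10 only in connection with HES. If ONS is meant to contribute, the text needs to say so.
- *A GP may code the death.* A death outside hospital still counts if the GP record carries a listed Read code. The two lists are not reproduced, so how often this happens cannot be judged. The point concerns deaths that stay uncoded.
- *The objective is about diagnoses.* Objective 2 speaks of new diagnoses and places all-cause mortality beside them, so these deaths are not lost to the study. That is correct. Adding ONS causes broadens the event definition. All-cause mortality, however, mixes them with every other cause and does not answer the CHD or stroke hypothesis.
- *Reach of the remedy.* The unlinked analysis cannot use ONS. Earlier coding of CHD in attenders who do not die would raise their recorded incidence with or without ONS data.

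A reader might infer that the protocol censors these people as event-free at death. It does not say so. The only censoring rule stated is for controls who later have a check, and the handling of death may be left to a SAP. A reader might also infer that the power claim is wrong or that the ratios are biased. The documents support neither: the power reproduces, and the bias figures depend wholly on assumed inputs.

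**Conclusion.** The point holds as a gap in two primary outcome definitions. Read as written, CHD and stroke rest on CPRD Read codes and HES codes, unrecorded events are presumed absent, and the ONS cause of death has no stated part in either outcome. This is more than detail awaiting a SAP, because the protocol itself fixes the case definitions and the purpose of each linkage.

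The size is unknown. The stated power stands. A fall below 90% requires both that the 3 per 1,000 includes uncoded deaths and that roughly 6% to 13% of first events are missed. Bias in the ratio requires capture, or the effect of the check, to differ for these deaths. The figures above are sensitivity illustrations and not estimates. The change is worth making because the data are already requested.

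**What to change.** In Exposures, Outcomes and Covariates and in Table 1, for the linked analysis, define first CHD as the earliest of a listed Read code, a HES I20-I25 code or an ONS underlying cause of I20-I25. Define first stroke in the same way with I60-I64. Report fatal first events as a sub-type beside the existing ones. Under Limitations, state that the unlinked analysis can miss deaths with no GP code.

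The cost is a few lines of text. No extra data or patients are needed, because ONS mortality is already requested and already limits the linked population and period. There are two downsides: the linked and unlinked event definitions would differ slightly, and the certified cause of death can be misclassified. The sub-type report would let readers see how much the added deaths contribute.
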